### Objectives

#### Primary objective: Examine the feasibility of _HDS_EMG for rapid, non-invasive screening of XII nerve function.

We plan to show that a machine learning algorithm trained on features of _HDS_EMG waveforms collected during a brief series of tongue tasks will detect CN XII neuropathy and grade its severity on a continuous, more sensitive scale than existing EMG. Time-frequency features extracted from _HDS_EMG will be used to detect tongue neuropathy grade using linear discriminant analysis, ensemble machine learning classifiers, and a neural network with a multiclass activation function, providing insight into the relationship between _HDS_EMG and tongue function degradation. Tongue _HDS_EMG will also be decomposed into estimates of constituent MU spike trains for analysis with a convolutional neural network.

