### Needle electromyography and nerve conduction

Intramuscular EMG will assess insertional activity in the genioglossus muscle, innervated by CN XII, as a marker of denervation [23]. Needle EMG is reported to have an inter-operator reliability of 0.53 [24]. EMG recordings will be conducted by a cancer neurologist fellowship trained in clinical neurophysiology and denervation potentials graded per standard neurologist’s grading:

0 - None

1 - Persistent, single train of potentials in at least two areas

2 - Moderate number of potentials in three or more areas

3 - Many potentials in all areas

4 - Full interference patterns of potentials

EMG and NCS may also be performed in the trapezius muscle (innvervated by CN XI), as the region is easily accessible for non-invasive testing and represents a muscle within the irradiated field with lower cranial nerve innervation. Both quantitative and qualitative EMG may be assessed [25]. Needle EMG will not be conducted if platelets are < 50,000. The intramuscular EMG will require a clinical visit with the neurologist.

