### Outcomes definition

#### Primary objective.

For analysis of the primary objective, the primary endpoint will be _HDS_EMG classification of XII neuropathy (yes/no, then graded) in relation to the gold-standard needle EMG classification. We expect to show that features such as frequency of interference patterns and tongue fasciculations correlate between _HDS_EMG and needle EMG, demonstrating that _HDS_EMG is a feasible, rapid, non-invasive biomarker for tongue neuropathy. We will consider _HDS_EMG feasible for this exploratory analysis if more than 80% of the signal recordings meet the quality criteria. We also expect that a neural network with a multiclass activation function will grade tongue neuropathy progression on a continuous scale.

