All accepted signals are divided into 2-second segments for feature extraction. The Discrete Wavelet Transform (DWT) will be used to extract time series features (waveform length, zero crossings, slope signal changes, root mean square, autoregressive coefficient, mean absolute value, and integrated mean absolute value) and time-frequency features (mean instantaneous frequency, mean first derivative, amplitude-modulated bandwidth, frequency-modulated bandwidth, and spectral moment of power spectral density) [32]. We will perform Mann—Whitney U-tests with α = 0.05 to determine whether these features are relevant to neuropathy through the following comparisons: reduced recruitment vs. no reduced recruitment; polyphasia vs. no polyphasia; increased amplitude vs. no increased amplitude; and increased duration vs. no increased duration. To further demonstrate the clinical relevance of _HDS_EMG features, we will use Pearson’s Correlation Coefficients and multiple regression analysis to express correlations between _HDS_EMG features and tongue functional outcomes (L-ROM and IPOI pressure).

The full dataset will be partitioned patient-wise into 70% for training, 20% for development, and 10% for validation. Features from the training set that discriminate neuropathy severity will be selected using linear discriminant analysis. Missing data may occur during time-frequency feature extraction, as some calculations can trigger divide-by-zero errors, especially for low-frequency components. If this occurs, such examples will be rejected as artifacts. If any class label is represented by less than 10% of the data, recording-wise mean imputation will be performed to augment the number of unique examples in the underrepresented classes.

We intend to train an initial decision tree and support vector machine (SVM), followed by ensemble methods using both trees and SVMs, where possible: Random Forest Classifier, Gradient Boost, and Bagging. We will also train a neural network classifier with a softmax activation function for multiclass classification. Hyperparameter optimization will be performed using 5-fold cross-validation and verified using the development set. To account for potential class imbalance, all ensembled learning methods will be trained using class-weighted sampling to ensure that individual classifiers within the ensemble see class-balanced subsets of the data. Machine learning will be performed using SciKit Learn [33].

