### Evaluation criteria

The performance of machine learning classifiers will be divided into two classification settings: binary (CN XII neuropathy vs. no confirmed CN XII neuropathy) and multiclass (neuropathy grade). In binary classifiers, we aim for AUC ≥ 0.70 to support _HDS_EMG as an inexpensive, non-invasive quantitative metric for screening OPC survivors for CN XII neuropathy. Narayanaswami et al. report that electromyographers with 10–20 years of experience have a diagnostic sensitivity of 0.77 and a specificity of 0.71 for neuropathy. [24] This will serve as our benchmark for reliable performance for all binary model development. For the 10% validation set, we will measure model performance simply by the percentage of correctly diagnosed cases of neuropathy. As a secondary validation outcome, we will compare the _HDS_EMG neuropathy severity grade with the gold-standard needle EMG grades.

Multiclass classification will use micro- and macro-F1 scores to evaluate the validity of a refined CN XII neuropathy grade prediction. Saliency mapping for the CNN will reveal which signal regions contribute to each neuropathy grade prediction. Machine learning models will be evaluated using SHapley Additive exPlanations (SHAP) to investigate which features contribute to the model predictions [39].

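### The plan promises a continuous, more sensitive severity scale than needle EMG, but the only statistic named for grading, F1, ignores grade order and cannot assess a continuous score

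*Protocol article*

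**What the plan says.** **The promise.** Under Objectives, the primary objective is that the algorithm will detect neuropathy and "grade its severity on a continuous, more sensitive scale than existing EMG". The Outcomes definition for the same objective makes grading the second step of the primary endpoint, judged against needle EMG, and expects that "a neural network with a multiclass activation function will grade tongue neuropathy progression on a continuous scale".

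**The reference.** The needle EMG section lists five ordered grades, from 0 (none) to 4 (full interference patterns).

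**The models.** The Data analysis and machine learning plan names trees, support vector machines and ensembles, and adds: "We will also train a neural network classifier with a softmax activation function for multiclass classification". A convolutional network is also trained to predict the grade. The Fig 1 caption mentions a final multitask network without describing its output.

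**The evaluation.** For grading, the Evaluation criteria state: "Multiclass classification will use micro- and macro-F1 scores to evaluate the validity of a refined CN XII neuropathy grade prediction". As a secondary validation outcome, "we will compare the _HDS_EMG neuropathy severity grade with the gold-standard needle EMG grades"; no statistic is given for this comparison. HDsEMG features are separately correlated with, and regressed on, lingual range of motion (L-ROM) and IOPI tongue pressure.

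**The concern.** There are two mismatches between aim and evaluation.

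1. **Scale.** The aim is a continuous severity score. F1 is computed from hard class assignments, and calling a true grade 0 a grade 4 costs the same as calling it a grade 1. No continuous score is defined, and no named statistic would assess one.

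2. **More sensitive than needle EMG.** The model output is trained on needle EMG and scored against it. Agreement with a reference can at best be complete; it cannot show that the new scale improves on the reference.

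The graded half of the primary endpoint could therefore be reported without showing whether the score follows severity. The superiority statement could be carried into the results without any analysis able to support it.

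**Working it through.** The protocol states no figure for graded performance, so there is nothing to reproduce. Two checks were made.

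**Check 1: does F1 see the order of the grades?**

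Inputs: N = 36 (protocol). Assumed grade mix, for illustration only: 26, 3, 3, 2 and 2 patients in grades 0 to 4. Each model makes six errors.

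- Model A (all adjacent): two 0→1, two 1→0, one 3→4, one 4→3.
- Model B (mostly distant): two 0→1, one 1→3, one 1→4, one 3→0, one 4→0.

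In both models each grade has the same numbers of hits, false positives and false negatives. Class F1 = 2TP/(2TP + FP + FN):

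| Grade | TP | FP | FN | F1 |
|---|---|---|---|---|
| 0 | 24 | 2 | 2 | 0.923 |
| 1 | 1 | 2 | 2 | 0.333 |
| 2 | 3 | 0 | 0 | 1.000 |
| 3 | 1 | 1 | 1 | 0.500 |
| 4 | 1 | 1 | 1 | 0.500 |

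- Micro-F1 = 30/36 = 0.83 for both.
- Macro-F1 = 3.256/5 = 0.65 for both.

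Quadratic-weighted kappa = 1 − (observed squared grade differences)/(those expected by chance). The chance term is Σ nᵢnⱼ(i−j)²/36 = 3622/36 = 100.6 for both models.

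- A: 6 × 1 = 6, so kappa = 1 − 6/100.6 = 0.94.
- B: 1 + 1 + 4 + 9 + 9 + 16 = 40, so kappa = 1 − 40/100.6 = 0.60.

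The result does not depend on the uneven mix. Take ten cases per grade, three of each ten wrong, and wrong labels spread so that every grade also receives three false positives. F1 is then 14/20 = 0.70 for every pattern. The chance term is 200.

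- Nearer errors (0→1, 1→0, 2→3, 3→4, 4→2): 3 × (1+1+1+1+4) = 24, kappa 0.88.
- Farther errors (0→3, 1→4, 2→0, 3→1, 4→2): 3 × (9+9+4+4+4) = 90, kappa 0.55.

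**Check 2: can scoring against needle EMG show better detection?**

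Inputs: sensitivity 0.77 and specificity 0.71, the figures the Evaluation criteria cite for experienced electromyographers; prevalence 40%, the plan's post-treatment expectation. Assumption: the cited rates apply to the needle EMG reference used here.

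For an error-free HDsEMG test scored against that reference:

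- Apparent sensitivity = 0.40×0.77/(0.40×0.77 + 0.60×0.29) = 0.308/0.482 = 0.64.
- Apparent specificity = 0.60×0.71/(0.60×0.71 + 0.40×0.23) = 0.426/0.518 = 0.82.
- Agreement = 0.308 + 0.426 = 0.73.

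At 42% prevalence the three values are 0.66, 0.81 and 0.74; at 5% they are 0.12, 0.98 and 0.71. A test that only copied needle EMG would score 1.00 throughout.

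**Finer resolution.** Needle EMG takes five values. Two patients with the same needle grade but different scores have no needle-based truth to separate them, so a gain in resolution within a grade is also invisible to this reference.

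**The case against.** The strongest replies are these.

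- **Meaning of more sensitive.** The Introduction criticises needle EMG for its coarse, subjective grading, so the phrase may mean finer resolution rather than diagnostic sensitivity. This stands as a reading. Check 2 addresses detection only, but the resolution reading fails for the reason given at the end of the working.
- **Softmax outputs are continuous.** True: a continuous score can be derived from them. The plan gives no rule for doing so, and F1 would not assess the result. The output of the final multitask network is not described, so one should not infer that the final prediction must be unordered.
- **Other analyses exist.** The severity comparison with needle grades could use an order-aware statistic. It names none and keeps needle EMG as the standard. The L-ROM and IOPI analyses are independent of the needle but use features, not predicted severity.
- **F1 is not meaningless.** High micro- and macro-F1 do require correct grades. Predicting grade 0 for everyone in the assumed mix gives micro-F1 26/36 = 0.72, but macro-F1 of only (52/62)/5 = 0.17, so the planned pair exposes that failure.
- **The study is exploratory.** The protocol says so, and no F1 threshold drives a conclusion. That limits the consequences; it does not support a superiority aim with no matching analysis.

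A reader might infer that neither promise could ever be tested in this study. The documents do not support that: the limit lies in the evaluation as written. The planned model output and functional measures would allow an order-aware assessment and an exploratory look beyond needle EMG.

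**Conclusion.** The point holds for the evaluation as written. The only statistics named for the graded endpoint ignore order and require hard labels, so they cannot show that a continuous score tracks severity. No planned analysis of the model output can show a scale more sensitive than needle EMG, on either meaning of the phrase.

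The size is illustrative. Equal F1 can accompany weighted kappa of 0.94 or 0.60, under a grade mix that the protocol does not supply. F1's blindness to order needs no assumption. The 0.64 apparent sensitivity of an error-free test rests on the cited accuracy figures applying here and on 40% prevalence. This should be corrected, but it does not undermine the binary AUC target or the recording-quality criterion.

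**What to change.** 1. Define the continuous score: the expected grade, Σ(grade × class probability), or an ordinal output.
2. Make the graded criterion either Spearman correlation of that score with needle grade, or quadratic-weighted kappa. Keep micro- and macro-F1 as secondary.
3. Compute it per patient on pooled out-of-fold predictions from patient-wise folds, with a patient-level bootstrap confidence interval. The 10% validation set is only 0.10 × 36 = 3.6, about 4 patients, too few for either statistic.
4. Replace the claim of greater sensitivity with agreement with needle EMG. Alternatively, label it a hypothesis, explored by correlating the score with IOPI pressure and L-ROM within needle grades, and state that the estimates will be imprecise.

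The cost is plan wording and a little code. The measures are already planned, and data collection runs to May 2027, so the change can be made before the final analysis. The downside is a dropped aspirational claim and a wide interval at N = 36.

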### Patient and public involvement

Patients and the public were not involved in the design. However, the investigators have recently engaged patient research partners for a program of research on delayed oropharyngeal cancer sequelae and expect to involve participants in the implementation and dissemination of the research plan, including consultation on recruitment/data collection strategies and on integrating these technologies into clinical trials.

### Dissemination strategy

Research data collection began in June 2024. Data collection will continue through May 2027, and we are targeting December 2027 for completion of data analysis. We will perform preliminary analyses and report progress in the annual RPPRs associated with this study’s NIH funding. We expect to submit our complete findings to a suitable journal by March 2028. We will disseminate the findings of our analysis to the scientific and medical community through publication in a peer-reviewed journal and presentation at relevant conferences for head and neck surgery, electrodiagnostics, biomedical engineering, and machine learning.

## Discussion

This study will primarily investigate the feasibility of tongue _HDS_EMG to monitor CN XII neuropathy in OPC survivors. Clinical gold-standard functional and neurophysiological data will be collected alongside experimental data to provide a diverse set of correlatives that strengthen the clinical relevance of the experimental findings. By synchronizing gold-standard needle EMG, _HDS_EMG, and machine learning methods for time series signals, our analysis will elucidate relationships between morphology and the continuum of nerve health and function in OPC survivors. Comparisons between electrodiagnostic methods, functional outcomes, and patient-reported outcomes will reveal links between underlying physiology and tongue functional degradation. Oropharyngeal cancer survivors’ outcome data will be collected into a central database, with access available upon request, facilitating research collaboration.

Our long-term goal is to provide a simple quantitative metric to detect loss of neurophysiologic signal in the tongue, thereby stratifying those at risk for profound late-effect syndromes earlier in their survivorship. Should this _HDS_EMG neurophysiologic marker prove possible, it may allow doctors to employ simple pharmacologic solutions such as early pulsed, high-dose steroids (e.g., similar to the Bell’s palsy model or use in radiation-induced optic nerve injury) [40,41] that depend on early detection to avoid the functional catastrophe of subsequent muscle atrophy and aberrant reinnervation.

The collected data may fail to demonstrate that _HDS_EMG feature machine learning classification adequately detects XII neuropathy, in which case, concurrent EIM offers a compelling alternate non-invasive biomarker for denervation-mediated compositional changes that we will also collect in this protocol [16,17].

Fundamentally, if the data fail to show that _HDS_EMG features can be used to train machine learning classifiers to screen for XII subclinical neuropathy, the comprehensive follow-up of the cohort remains compelling. That is, linking the EMG denervation classification with functional outcomes (e.g., IOPI, L-ROM, and PROs) alongside non-invasive EIM as a physical compositional tongue measure will allow estimation of prevalence, functional translation, as well as comprehensive hypothesis-generating analyses of post-RT lingual denervation in a manner explored for other nerves but not yet quantified for radiation-associated CN XII [42].

This protocol seeks to provide technical solutions and mechanistic insight to refine management of just one domain of HNC survivorship (neural-mediated radiation-associated dysphagia). However, the work must be taken in the broader context of the rapidly evolving landscape of HNC, where progress in tumor microenvironment, immunotherapy, optimized radiation, and targeted therapy promise to transform care models. Comprehensive, mechanistically informed multidimensional toxicity assessments will be one of many advances the investigators hope to realize in the next generation of head and neck cancer care. For example, we recognize the role of the CXCL12-CXCR4 signaling axis in cancer metastasis and the utility of nanomedicine strategies to enhance immunogenic cell death to improve immunotherapy efficacy [43–45]. If successful, methods for non-invasive hypoglossal nerve monitoring will need to be integrated with similar emerging multidimensional protocols for other toxicity states, such as radiation-induced ocular complications and mental health care during cancer treatment [46–48].

We acknowledge that only exploratory interpretations can be made from models trained on patients at a single site and evaluated by a single physician. Additionally, several other factors, such as primary tumor site, radiation dose, chemotherapy, and time since radiation treatment, are not controlled for in this study. We intend to investigate only the diagnostic utility of _HDS_EMG and EIM, but we cannot comment directly on factors that contribute to the risk of CN XII neuropathy. Future work may include a follow-up study stratifying patients by radiation dose to control for its influence on LCNP risk. The effects of radiation and chemotherapy on neuropathy incidence have also been studied within our group and may be replicated with respect to _HDS_EMG. [48,49] The generalizability of our work will be limited by our exploratory sample size of N = 36. Future work would involve patients at multiple sites and use a group of physicians to evaluate needle EMG. Additionally, _HDS_EMG analysts would be blinded to the labeled diagnosis of a multi-site test set of patients to further validate generalizability. Our work will inform future sample size estimates by establishing benchmark sensitivity and specificity values for neuropathy classification using _HDS_EMG.

## Conclusion

We hypothesize that tongue _HDS_EMG analysis, paired with time-frequency feature extraction, MU decomposition, and machine learning, will be feasible for monitoring CN XII health in OPC survivors at risk for CN XII neuropathy. Such a tool would provide a non-invasive means for quantitative diagnosis and monitoring of CN XII neuropathy.
